## Methods

### Aims and Hypotheses of the Study

In ci-chimps, we aim to determine if three implementation interventions are helpful in improving the clinical implementation of the CHIMPS-NET interventions. Additionally, we want to identify factors hindering or promoting implementation processes. In order to monitor the impact of the three implementation interventions, we will use the translated version of the “Family Focused Mental Health Practice Questionnaire (FFMHPQ)” (26) and the translated version of the “Implementation Components Questionnaire (ICQ)” (28). The introduction of these questionnaires in Germany has not yet been reported. So the aims of the study are 1) the cultural and linguistic adaptation of the “Family Focused Mental Health Practice Questionnaire” (26) and the “Implementation Components Questionnaire” (28) from English to German, 2) the first introduction of these questionnaires in Germany, 3) the evaluation of the effect of the three implementation interventions in CHIMPS-NET, and 4) the identification of factors which hinder or promote implementation processes of family-oriented interventions using the example of CHIMPS-NET intervention.

More specifically, the following hypotheses will be tested:
H1: In this randomized controlled multicenter trial, we will compare the family-oriented practice between the clinical centers receiving the support of the three implementation interventions and the clinical centers not receiving the support of the implementation interventions. Our primary hypothesis is that clinical centers receiving at least one of the implementation interventions work more family-oriented than clinical centers without the support. Higher values after 12- and 24-months follow-up compared to the baseline mean a higher family-oriented practice. This is measured with the translated version of the “Family Focused Mental Health Practice Questionnaire.”H2: Furthermore, with our secondary hypothesis, we will compare the personnel's satisfaction regarding the implementation of the CHIMPS-NET project between the clinical centers receiving additionally the support of the three implementation interventions and the clinical centers not receiving the support of the implementation interventions. The personnel's satisfaction regarding the implementation of the CHIMPS-NET project is higher in the clinical centers receiving the implementation interventions than the personnel's satisfaction in the clinical centers without the three implementation interventions. This is measured with the translated version of the “Implementation Components Questionnaire” where higher values mean higher personnel satisfaction.

### Study Design

As you can see in Figure 2 the ci-chimps study is a two-group randomized controlled multicenter trial with assessments at baseline as well as at 12- and 24-months follow-up. It is one part of the superior project CHIMPS-NET, wherefore an own study protocol is in preparation (9). The ci-chimps study will be conducted from January 2020 to September 2023. The ci-chimps project's preparation phase includes the translation of the questionnaires FFMHPQ and the ICQ and the randomization of the clinical centers. The first measurement (baseline) takes place from January 2020 to May 2021. We stopped the baseline assessment after the last implementation intervention and defined this point as the end of the implementation interventions. During this year we implemented the superior project CHIMPS and the three implementation interventions of ci-chimps in the clinical centers. The second assessment will be in May 2022 and the follow-up in May 2023.

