### Statistical Analysis

#### Data Coding and Analysis

All statistical analyses will be performed with SPSS (version 26.0 or newer). Means and standard deviations or median and 1st and 3rd quartiles, as appropriate, for the continuous variables as well as absolute and relative frequencies for the categorical variables of the whole sample and the respective treatment groups will be calculated and presented. The primary analysis will be conducted with the intention to treat (ITT) population consisting of all employees. The employees of a clinical center are subject to the same influences and cluster effects. Hence, for the primary endpoint, operationalized as the difference to baseline, a mixed linear model will be performed with treatment group, time, and baseline value as fixed effects, and clinical center as a random effect. The interaction between the treatment group and time will be tested and will be eliminated from the model if it is not statistically significant. The result of the primary analysis is the contrast of the treatment group after 18 months. Only this result will be considered in a confirmatory manner. The two-sided type I error will be set to 5%. It is possible that the fluctuation of employees in the clinical centers is so low that we can extend the model to a longitudinal model. The secondary endpoints will be examined in an exploratory manner with the same model in the case of continuous endpoints and with a similarly mixed Poisson regression in the case of count data. Results will be reported and published according to the CONSORT statement for cluster randomized trials (34).

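### Baseline questionnaires could be answered after the interventions had begun, and the primary model relies on that baseline

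*Protocol article*

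**What the plan says.** Study Design in the protocol article gives the calendar: "The first measurement (baseline) takes place from January 2020 to May 2021". It then says how the window was closed: "We stopped the baseline assessment after the last implementation intervention and defined this point as the end of the implementation interventions". The next sentence places delivery in the same period: "During this year we implemented the superior project CHIMPS and the three implementation interventions of ci-chimps in the clinical centers". Allocation was settled beforehand, since "The ci-chimps project's preparation phase includes the translation of the questionnaires FFMHPQ and the ICQ and the randomization of the clinical centers". For the later waves, "The second assessment will be in May 2022 and the follow-up in May 2023", which is 12 and 24 months after the close of baseline.

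Data Coding and Analysis builds the confirmatory analysis on this baseline: "for the primary endpoint, operationalized as the difference to baseline, a mixed linear model will be performed". The baseline score also enters that model as a covariate, next to group and time, and centers are random. Hypothesis H1 also reads benefit as follow-up values above baseline. Continuous secondary endpoints use the same model.

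The article contains no rule that a center or an employee had to complete the baseline form before the first referrer mailing, webinar or screening at that center. It contains no rule for flagging or setting aside forms completed later.

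**The concern.** A baseline covariate is harmless in a randomized comparison because treatment cannot have affected it. Here that is not secured. Centers were already allocated and delivery ran inside the baseline window, so an employee of an intervention center could have attended a webinar or begun screening before answering the baseline form. Control centers receive none of the three interventions, so such exposure can raise baseline in one arm only. (The parent project was also introduced in this period, but in both arms.)

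If the interventions work quickly, part of their effect then sits in the baseline and is taken out of the primary contrast. An early effect is plausible: the training is a three-hour program on knowledge and skills, and the FFMHPQ asks about both. The fitted model has no term that separates exposed from unexposed baselines. What is at stake is an understated or missed effect on the only result to be read as confirmatory.

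**Working it through.** **Inputs from the article** (Sample Size and Power Calculation; Randomization): d = 0.4, two-sided alpha 5%, power 80%, ICC 0.05, 18 centers, 31 employees per center, 30% incomplete questionnaires, realized allocation 8:10.

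**Assumed inputs, not in the article:**
- f: share of intervention-arm baseline forms answered after exposure
- e: share of the full effect already present in those forms
- b: within-arm slope of the follow-up score on baseline

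**Step 1. Reproduce the planned size.**
- Design effect: 1 + (31 − 1) × 0.05 = 2.5.
- With 9:9 centers, SE = √[(2.5/31) × (1/9 + 1/9)] = 0.134, and 0.4/0.134 = 2.99.
- The noncentral t with 18 − 2 = 16 df gives power 0.801. With 30 per center it is 0.796, so 31 is the smallest number that reaches 80%.
- 31 × 18 = 558, and 558/0.70 = 797.1, rounded up to 798. Both planned figures are reproduced.
- At 8:10, SE = √[(2.5/31) × (1/8 + 1/10)] = 0.1347 and power is 0.796.

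**Step 2. Expected contrast.** Exposure raises the mean intervention-arm baseline by f × e × d. A model for change with baseline as covariate gives the same treatment coefficient as a model for the follow-up score with baseline as covariate. The expected contrast is therefore d × (1 − b × f × e). A simulation with e = 1 agrees: at f = 0.5 both forms of the model gave 0.302 with b near 0.5 and 0.262 with b near 0.7, against 0.30 and 0.26 from the formula.

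**Step 3. Power.** A slope b that transmits the bias also reduces residual variance, so both must enter. I assume equal variance at baseline and follow-up, linked individual baselines, and both variance components reduced by 1 − b². Then SE = 0.1347 × √(1 − b²), which is 0.1167 for b = 0.5 and 0.0962 for b = 0.7 (8:10, 31 per center, 16 df).

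| f | e | b | Expected contrast | Power | Power with clean baseline |
|---|---|---|---|---|---|
| 0 | any | 0.5 | 0.40 | 0.90 | 0.90 |
| 0 | any | 0.7 | 0.40 | 0.97 | 0.97 |
| 0.25 | 0.5 | 0.5 | 0.4 × (1 − 0.0625) = 0.375 | 0.85 | 0.90 |
| 0.5 | 1 | 0.5 | 0.4 × (1 − 0.25) = 0.30 | 0.68 | 0.90 |
| 0.5 | 1 | 0.7 | 0.4 × (1 − 0.35) = 0.26 | 0.72 | 0.97 |

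**The case against.** The strongest reply is that the article gives study-wide windows only. With rolling delivery, baseline can close after the last intervention in the network even though every center was surveyed before its own first activity. The description of the training project lists an assessment of the current state alongside the training, which fits surveying first, and the study-design figure is not available here. This stands. A reader might infer that late responders in the intervention arm had in fact been exposed. The document does not show that, and f = 0 remains possible. What it shows is that nothing prevents exposure.

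Two further inferences go too far:
- Subtracting baseline and also adjusting for it might seem to remove the effect twice. It does not; with the covariate in the model there is a single loss of b × f × e × d.
- Putting 0.30 or 0.26 into the unadjusted SE of 0.1347 gives power of 0.55 or 0.44. That uses b for the bias but ignores the variance it removes. The consistent figures are 0.68 and 0.72.

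It can also be said that the statistics and discussion sections leave open whether the same employees answer each wave, so the baseline value may have to be a center-level quantity. That changes b and the precision, but a center mean built from exposed forms is still raised.

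Finally, a date rule may exist in an analysis plan not shown. But the article itself fixes the baseline window, and as written it admits post-exposure forms.

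**Conclusion.** The point holds as a gap in protection. The plan allows intervention-arm baselines to be collected after exposure and then relies on them in the primary endpoint and model. If that happened and the interventions act early, the contrast is attenuated. With no true effect, this mechanism produces no false positive.

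The size cannot be derived from the article. Under the assumptions shown, the expected contrast lies between 0.375 and 0.26 instead of 0.40. The power loss runs from about 4 percentage points in the mild case to about 22 to 26 points when half the forms carry the full effect. The latter case assumes that the whole effect appears at once, and a slower effect shrinks the loss in proportion. I am confident about the overlap in calendar time and the direction of any bias, but not about its presence or amount.

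**What to change.** Baseline collection is described as finished, so the change is to the analysis rules:

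1. Count as baseline only questionnaires dated before the center's first implementation activity (referrer mailing, webinar or screening). Apply a matched calendar cut-off to control centers.
2. Make the follow-up FFMHPQ score the outcome, with the pre-exposure baseline as covariate; use the center mean where individuals cannot be linked. Given the same baseline covariate, the treatment coefficient equals that of the change-score model. Employees without a valid baseline form stay in the analysis, whereas under the present endpoint they would have no change score.
3. Add a sensitivity analysis of follow-up scores without baseline adjustment.
4. Report the share of intervention-arm baseline forms completed after exposure.

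This needs questionnaire dates and center activity dates, assuming both were recorded, and new wording for the endpoint. The cost is fewer usable baseline values and some precision, by an amount that depends on f. The unadjusted comparison has power 0.796 under the planning assumptions, less than the 0.85 of the present model in the mild case above. It trades power for freedom from this bias, which is why it belongs as a sensitivity analysis.

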**Figure 2 F2:**
[figure not shown]
Study design.

### Study Setting

At the beginning of the study, 21 clinical centers located in 15 federal states in Germany were part of the CHIMPS-NETwork. Each clinical center has two subordinate clinics: one of the children and adolescent psychiatric department and one of the adult psychiatric department. Only 19 of the 21 clinical centers were randomized such that nine centers will receive additional support of all of the three implementation interventions (intervention group), and the remaining 10 clinical centers will be the control group and will not get specific implementation support. Hamburg (University Medical Centre Hamburg-Eppendorf, Germany), as the headquarter, and Munich (University Medical Center, Department of Psychiatry and Psychotherapy, Munich, Germany) are conducting their own study) are not randomized. Unfortunately, one clinical center of the intervention group left the study after a few weeks, so eight clinical centers remain in the intervention group and 10 in the control group. Because we defined the number of cases per clinical center, the unequal allocation to the intervention and control group leads to the consequence that the number of cases is different for the intervention- and the control group (TAU) as seen in Figure 1.

### Participants

#### Sample Size and Power Calculation

This study will be conducted in 18 clinical centers and 31 employees on average per clinical center will be required to detect a difference at 12 and 24 months follow-up regarding family-oriented practice measured with FFMHPQ between the clinical centers receiving the support of the three implementation interventions and the clinical centers not receiving the support of the implementation interventions of 0.4 (Cohen's d) with 80% power, a two-sided alpha of 5% and a cluster effect of 5% (intraclass correlation coefficient of 0.05). This results in a sample size of 558 employees (31 per clinical center). Assuming a proportion of 30% incompletely completed questionnaires, we aim to recruit 798 employees.

#### Randomization

The random allocation of the clinical centers that receive or do not receive the support in a ratio of 1:1 was conducted according to a central randomization list generated with the statistical software R version 3.6.3 by the Department of Medical Biometry and Epidemiology (University Medical Centre Hamburg-Eppendorf, Germany) outside the recruitment and clinic. Originally, 18 centers participated in the study. After the randomization, another center was recruited. This center was randomized individually. At the end of this procedure, one center withdrew its participation in the study. So, we have an allocation ratio of 8:10.

#### Criteria for Inclusion

Every employee involved in the treatment of the patients (Medicine, Psychology, Nurses) of every clinical center that is part of the CHIMPS-NET project will be invited to participate in the ci-chimps study.

#### Criteria for Exclusion

There are no explicit criteria for exclusion.

### Outcome Measures

#### Sociodemographic Questions

Besides age, gender and profession, we record with a specifically designed questionnaire, in which clinical center the employees work, how long they have been employed there and how strongly they are involved in the CHIMPS-NET-project.

#### Family Focused Mental Health Practice Questionnaire (FFMHPQ)

The “Family Focused Mental Health Practice Questionnaire (FFMHPQ)” (29) has 18 subscales, comprising a total of 53 items and measures numerous aspects relevant for family-oriented practice from the employee's point of view, on a 7-point Likert scale (ranging from strongly disagree to strongly agree plus “not applicable”). In addition to organizational and political aspects (e.g., workplace support, guidelines, local conditions, workload), the questionnaire determines the needs of hospital employees (e.g., knowledge transfer, skills about family issues, their interest in working with children, parents, and families) and families (e.g., psychoeducation). It also takes into account “external” factors such as the general organization of the health system and geographical conditions, as well as socio-demographic data. The Cronbach's alpha coefficients of the FFMHPQ range from 0.70 to 0.90 for most subscales. The FFMHPQ has demonstrated excellent face and content validities (29).

#### Implementation Components Questionnaire (ICQ-35)

In ci-chimps, we are using the shorter version of the “Implementation Components Questionnaire (ICQ-35)" (30). The 35 items questionnaire has nine subscales with five choices of response: “not applicable, yes, sometimes, no, don't know.” The employees are asked to rate their perceived level of integration of the intervention within their clinical center. It determines special components of implementation, like selection or training of the employees. The Cronbach's alphas of the subscales range from 0.67 to 0.83. The original long version of the ICQ has 89 items and was first adapted in Norway (31, 32) from an earlier version of the Measures of Implementation Components of the National Implementation Research Network Frameworks by Ogden et al. (31) and Fixsen et al. (32). It has been shown to have good psychometric validity (32).

#### Implementation Satisfaction Scale (ISS)

Additionally, we are using the 4 item “Implementation Satisfaction Scale (ISS)” (30) which is part of the ICQ. It measures how satisfied the employees are with the implementation process on a 5-point Likert scale (ranging from strongly disagree to strongly agree). The Cronbach's alpha of the implementation satisfaction scale is 0.88 (30).

### Translation Procedure

Up to now, the FFMHPQ has been used in different settings (e.g., family helplines, adult psychiatry) in various occupational groups (e.g., nurses, doctors) in Australia, Portugal, Thailand, Japan, Ireland, and Norway. The introduction of this questionnaire in Germany is still missing. The same applies to the ICQ and ISS. Adapting the FFMHPQ, the ICQ and the ISS to Germany should enable more effective implementation of family-oriented interventions in the regular healthcare system in the future.

According to the cross-cultural translation procedure recommended by Beaton and Guillemin (33), the questionnaires are translated from English to German and back into English. Two translators with German as their first language independently translate the questionnaire from English to German. Both versions (T1 and T2) are compared, differences are discussed and a third combined version T12 (synthesis from both translations) is developed. In the next step, two translators with English as their first language translate the questionnaire version T12 from German back into English (BT1 and BT2). Subsequently, the original questionnaires, the versions T1, T2, T12, BT1, and BT2 as well as the interim reports are discussed and evaluated within the framework of an expert committee. As a final step in the adaptation process, clinic employees are asked how they interpret the items and evaluate the questionnaire (applicability test). All questionnaires were slightly modified or reworded to adapt them to our target group.

### Statistical Analysis

#### Data Coding and Analysis

All statistical analyses will be performed with SPSS (version 26.0 or newer). Means and standard deviations or median and 1st and 3rd quartiles, as appropriate, for the continuous variables as well as absolute and relative frequencies for the categorical variables of the whole sample and the respective treatment groups will be calculated and presented. The primary analysis will be conducted with the intention to treat (ITT) population consisting of all employees. The employees of a clinical center are subject to the same influences and cluster effects. Hence, for the primary endpoint, operationalized as the difference to baseline, a mixed linear model will be performed with treatment group, time, and baseline value as fixed effects, and clinical center as a random effect. The interaction between the treatment group and time will be tested and will be eliminated from the model if it is not statistically significant. The result of the primary analysis is the contrast of the treatment group after 18 months. Only this result will be considered in a confirmatory manner. The two-sided type I error will be set to 5%. It is possible that the fluctuation of employees in the clinical centers is so low that we can extend the model to a longitudinal model. The secondary endpoints will be examined in an exploratory manner with the same model in the case of continuous endpoints and with a similarly mixed Poisson regression in the case of count data. Results will be reported and published according to the CONSORT statement for cluster randomized trials (34).

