## Discussion

While research has identified good evidence-based family-oriented interventions like CHIMPS that improve the quality of life of families, little is known about how to implement such interventions most effectively and efficiently in clinical practice in Germany. A strength of this ci-chimps -study is the use of a randomized controlled multicenter trial design with a large and wide-ranging sample. We are including both the child and adolescent as well as adult psychiatric departments and all professionals within a clinical center to get a better understanding of the implementation barriers. It could be a limitation that we can't ensure that the same employees fill out all four measurement times. For the first time in Germany, the translated versions of the questionnaires FFMHPQ and ICQ are used in Germany, so there is no German psychometric data yet. However, both original versions have demonstrated good psychometric validities in previous studies. Thus, it can be assumed that the translated German versions will show good psychometric validities as well.

Generally, it should be considered that ci-chimps is a purely questionnaire-based study, relying on the principle of self-disclosure. Therefore, the tendency toward social desirability cannot be ruled out. However, it can be assumed that this potential trend does not significantly affect the results, because the focus is on the comparison between employees from different clinical centers and the probability is high that this tendency can be found for both groups.

With ci-chimps, the implementation of CHIMPS is being supported for the first time. In previous studies of CHIMPS, there were no specific implementation interventions. Therefore, it should be considered that we can only measure an overall intervention effect. It is not possible to compare the three implementation interventions amongst each other. However, we are sure that with ci-chimps we will be able to identify training needs in clinics in order to improve the implementation of family-oriented interventions like CHIMPS-NET in the future.

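### The primary endpoint is a difference to baseline in all employees, but the plan cannot ensure that the same employees answer at each wave, and the sample size has no margin for unmatched staff

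*Protocol article*

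**What the plan says.** In the protocol article, Data Coding and Analysis sets the primary analysis in the "intention to treat (ITT) population consisting of all employees". The outcome is defined "for the primary endpoint, operationalized as the difference to baseline". The mixed linear model has treatment group, time and baseline value as fixed effects and clinical center as the only random effect. The section then says that an extension to a longitudinal model is possible if staff fluctuation turns out to be low. Only this primary contrast is confirmatory.

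The Discussion lists as a limitation that the authors cannot ensure that "the same employees fill out all four measurement times".

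Sample Size and Power Calculation states the requirement in employees: "This results in a sample size of 558 employees (31 per clinical center"), for a Cohen's d of 0.4 and an "intraclass correlation coefficient of 0.05". The only allowance for loss is this: "Assuming a proportion of 30% incompletely completed questionnaires, we aim to recruit 798 employees".

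Study Design places baseline between January 2020 and May 2021, with later assessments in May 2022 and May 2023.

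**The concern.** A difference to baseline, adjusted for the baseline value, needs two measurements on the same unit. If that unit is the employee, someone who joins after baseline has no baseline, and someone who leaves has no follow-up. Neither has an endpoint. The plan thus makes its confirmatory outcome depend on a link between questionnaires that it says it cannot ensure, while calling the analysis set all employees.

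Bias is the main risk. Staff who stay and answer twice are selected after the centers were randomized. Intervention centers receive training and screening tasks, so staying and responding need not be alike in the two arms. The contrast could then mix an effect on practice with differential retention.

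Precision is the lesser risk. The 30% is stated for incomplete questionnaires, and nothing is added for staff turnover between questionnaires that may lie 24 to 40 months apart (May 2021 or January 2020 to May 2023).

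**Working it through.** **Inputs from the protocol article.** d = 0.4, two-sided 5%, 80% power, ICC 0.05, 18 centers, 31 employees per center, 558 evaluable, 30% incomplete, 798 recruited (Sample Size and Power Calculation). Allocation 1:1, now 8:10 centers (Randomization).

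**Inputs assumed.** The share r of complete responders who can be matched across two waves, and the baseline to follow-up correlation ρ. The documents give neither, so ranges are shown.

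**Formula.** With m analysed employees per center and k₁, k₂ centers per arm: DEFF = 1 + (m − 1) × 0.05; SE = √[DEFF × (1/(k₁m) + 1/(k₂m))] in SD units; noncentrality = 0.4/SE; power from the noncentral t with 18 − 2 = 16 df.

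**Step 1: reproduce the plan.** At 9:9 and m = 31, DEFF = 1 + 30 × 0.05 = 2.5, SE = √(2.5 × 2/279) = 0.1339 and noncentrality = 2.988, so power is 80.1%. At m = 30 it is 79.6%, so 31 is the smallest sufficient size. Then 31 × 18 = 558 and 558/0.7 = 797.1, rounded up to 798. The stated figures reproduce exactly. At the actual 8:10, SE = √[2.5 × (1/248 + 1/310)] = 0.1347 and power is 79.6%.

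**Step 2: the margin.** 798 × 0.7 = 558.6 against 558. Once 30% are incomplete, nothing is left for unmatched staff.

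**Step 3: pairs and power at 8:10.** Pairs = 798 × 0.7 × r and m = pairs/18. Adjusted power multiplies the variance by 1 − ρ², applied to the whole variance as a simplification.

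| Matched r (assumed) | Pairs | m | DEFF | Power, unadjusted | Power, ρ = 0.3 | Power, ρ = 0.5 |
|---|---|---|---|---|---|---|
| 80% | 447 | 24.8 | 2.19 | 76.0% | 79.8% | 86.8% |
| 70% | 391 | 21.7 | 2.04 | 73.4% | 77.4% | 84.7% |
| 50% | 279 | 15.5 | 1.73 | 66.1% | 70.2% | 78.3% |

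The 70% row also equals 798 × 0.7 × 0.7, that is, 30% incomplete independently at each of two waves with no turnover.

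**Step 4: recruitment needed to keep 558 pairs.** 558/(0.7 × r) gives 997, 1,139 and 1,595 for r of 80%, 70% and 50%.

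**Step 5: the alternative reading of the 30%.** If it was meant to cover every loss, including turnover, then 798 × 0.7 = 558.6 pairs and the target is met.

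**The case against.** The article never says that the baseline is the employee's own. Center is the only random effect, and the longitudinal model is held back as an extension. The base model might therefore be a comparison of repeated cross-sections against a center-level baseline. On that reading every respondent could be analysed and turnover would cost no pairs. This stands as a possibility, but no center-level baseline is stated, while the sample size, the ICC and the analysis population are all expressed in employees.

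Centers were randomized, so all employees may simply mean analysis by the center's allocation, with missing data left to the analysis plan. That is fair as far as it goes. It does not give an endpoint to staff who were never measured at baseline.

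The pair counts above suit a contrast at one follow-up wave. If either follow-up suffices, as it could once the group-by-time interaction is dropped, 798 × 0.7 × (1 − 0.3²) = 508 employees contribute before turnover, and unadjusted power is about 78%. This also stands and makes the power loss smaller.

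A reader might infer that the primary analysis cannot be run, that the plan expects different staff at each wave, or that 558 will not be reached. The documents support none of these. The model can be fitted to matched staff. The authors say only that they cannot ensure the same respondents, and they consider low fluctuation possible. A shortfall below 558 follows only if matching losses come on top of the 30%, at a rate that the documents do not give.

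**Conclusion.** The point holds as a conflict between stated elements: a difference to baseline, an analysis set of all employees, and respondents who may change between waves. At employee level the confirmatory result would rest on staff present and responding at both times, a group formed after randomization that may differ by arm. This rests on the employee-level reading. If a center-level baseline was intended, the text must say so.

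The sample-size arithmetic is correct but has no margin for unmatched staff. The loss runs from about 4 percentage points of unadjusted power at 80% matching (79.6% to 76.0%) to about 14 at 50% (79.6% to 66.1%). At 391 pairs, baseline adjustment brings power to about 85% with a correlation of 0.5 and about 77% with 0.3. All of these rest on assumed matching and correlation. Power is therefore the secondary argument. The main one is that the endpoint and population of the only confirmatory test are not reconciled and could be settled after turnover has been seen.

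**What to change.** Before follow-up data are analysed, choose one of two routes.

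**Preferred: model the score.** Use the FFMHPQ score at each wave as the response in one mixed model. Fixed effects are wave and group-by-wave with a common baseline mean. Random effects are center, center-by-wave and, where responses can be linked, employee. Everyone who answers any wave then contributes, and 31 per center becomes the number needed at the primary wave. Department and profession may be added but are optional. The common mean is justified only for baseline questionnaires answered before the center received the interventions. This needs checking, because Study Design keeps baseline open until the last implementation intervention.

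**Alternative: a linked cohort.** Link employees, describe the analysis set as staff with baseline and follow-up rather than all employees, state how missing data are handled, and restate 558, 798 and the power for complete pairs.

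The first route costs a change of wording and a somewhat larger model. Its downsides are that unlinked respondents bring no precision gain from an individual baseline, and that later joiners who choose to respond remain a possible source of selection. The second route may require more recruitment (Step 4 of the working).

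Neither route settles the time of the primary contrast, given as 18 months although assessments are at 12 and 24. That must be reconciled separately.
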